#### Secondary

Secondary outcome measures include participants who had a four or greater reduction in POEM score (termed ‘responders’ [56]); the difference in POEM scores analysed per protocol; the difference in POEM scores; the difference in Patient Oriented SCORing Atopic Dermatitis (PO-SCORAD) [57]; the difference in pharmacist-assessed SCORing Atopic Dermatitis (SCORAD) score (part B only) [58]; withdrawals due to the exacerbation of eczema; the proportion of treatment escalation between groups; the difference in Dermatology Life Quality Index (DLQI) [59, 60]; participant acceptance of the treatment measured by Treatment Satisfaction Questionnaire for Medication (TSQM) Version II [61]; Numerical Rating Scale (NRS) of the acceptability of the treatment; the proportion of cutaneous and systemic events between the treatment groups; the difference in SCORAD scores between blinded pharmacist and blinded dermatologist; and the difference in SCORAD scores between pharmacists. For full schedule of interventions and assessments see Table 2*.*

#### Statistical analysis

Primary outcome analysis, and analysis of secondary POEM, PO-SCORAD, and DLQI outcomes will be by ANCOVA with baseline POEM score as a continuous covariate, and randomised treatment as a categorical variable of interest. Analysis of proportions will be by estimation of relative risk and associated confidence intervals. Participant acceptability will be assessed by t-test, or if normality assumptions are strongly violated by Mann–Whitney test with Hodges-Lehmann estimator of location. Comparison of SCORAD scores between pharmacists and between pharmacist and dermatologist will be by linear mixed model with participant treated as a random effect.

Analysis will be separated by intention-to-treat (ITT) and per protocol set (PPS), with ITT as the primary analysis. ITT population is all participants randomised. PPS is all participants with at least 80% completed data, including primary outcome with no significant protocol deviations determined to influence POEM score. For inclusion in PPS, participants should adhere to treatment instructions, measured by > 80% daily adherence. Missing outcome data will not be imputed. No interim analyses are planned and SAS will be used for analysis.

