**Methods:**

This multicentre, single-blind, parallel-group, randomised controlled trial aims to recruit 118 participants from community pharmacies in Aotearoa New Zealand. Participants will be randomised 1:1 to receive topical cream with 2% ECMT-154 or vehicle control, and will apply assigned treatment twice daily to affected areas for six weeks. The primary outcome is improvement in subjective symptoms, assessed by change in POEM score. Secondary outcomes include change in objective symptoms assessed by SCORAD (part B), PO-SCORAD, DLQI, and treatment acceptability assessed by TSQM II and NRS.

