### Randomisation and masking

Participants are randomised 1:1 to receive a 2% ECMT-154 cream or vehicle control. Participants will be block randomised, block size four, and randomisation will be stratified according to site. A computer-generated randomisation number sequence will be created by the study statistician. Randomisation of participants takes place at the pharmacy, electronically within REDCap. Participants will be randomised by pharmacy investigators who have no access to the randomisation schedule. Manufacturing and labelling of interventional treatments will be conducted by an external compounding pharmacist, licensed to complete such activities and assessed according to Good Manufacturing Practice guidelines. Active treatment and vehicle control will be labelled as “Treatment G” and “Treatment H” in non-descript packaging for the purpose of blinding. Study investigators at the pharmacies and MRINZ will be blinded. Participants will not be told if they receive the active or control cream, however due to the distinctive smell of ECMT-154 compared to control, participants are assumed to be unblinded therefore this study will conservatively be classified as single blind rather than double blind.

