### Participant timeline

Upon presentation to the pharmacy, consent, demographic data, eligibility, and baseline data are collected, followed by a clinical photograph of a representative eczema lesion, chosen by the participant. The participant is randomised, and the appropriate treatment is dispensed by the study pharmacist along with the aqueous cream. Over the six-week interventional period, participants complete a weekly digital diary to report POEM, treatment adherence, adverse events, and use of concomitant medications (Table 2). Participants return to the pharmacy for a second face to face visit at week six including a second clinical photograph of the representative lesion. A final electronic follow up survey is completed at week eight to collect any adverse events following the cessation of study treatment. The study flow is depicted in Fig. 1*.*

**Table 2 Tab2:** Summary of study procedures

	Visit 1	Treatment Period					Visit 2	Follow Up Survey
Day	**0**	**7**	**14**	**21**	**28**	**35**	**42 (+ 5)**	**14 days post Visit 2 (+ 5)**
Eligibility screen	X							
Informed consent	X							
Demographic data collection	X							
POEM	X	X	X	X	X	X	X	
PO-SCORAD	X						X	
SCORAD (Part B)	X						X	
DLQI	X						X	
Eczema photo	X						X	
Randomisation	X							
Dispense medication	X							
Electronic study diary		X	X	X	X	X		
Treatment compliance		X	X	X	X	X	X	
Adverse event collection		X	X	X	X	X	X	X
TSQM Version II							X	
Acceptability NRS							X

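### PO-SCORAD and DLQI are to be adjusted for baseline POEM although each scale's own baseline is collected; this costs precision in two secondary comparisons but introduces no bias on average

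*Protocol article*

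**What the plan says.** One sentence in the Statistical analysis section fixes the model for the primary outcome and for several secondary ones: "analysis of secondary POEM, PO-SCORAD, and DLQI outcomes will be by ANCOVA with baseline POEM score as a continuous covariate". The only other model term named is the allocated treatment. Baseline POEM is thus the stated covariate for PO-SCORAD and DLQI as well as for POEM.

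Under Participant timeline, the article says that at the first pharmacy visit "consent, demographic data, eligibility, and baseline data are collected". That phrase names no scale, but Table 2 in the same section does: it marks PO-SCORAD, SCORAD (Part B) and DLQI at day 0 and again at day 42.

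The Abstract describes these outcomes as changes: "Secondary outcomes include change in objective symptoms assessed by SCORAD (part B), PO-SCORAD, DLQI". The list of secondary outcomes speaks only of a difference in each score, so it is not certain whether the week-6 score or the change from baseline is modelled. Both are worked below.

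**The concern.** ANCOVA gains most when its covariate is the baseline of the outcome being analysed, because that is usually the best single predictor of the follow-up value. POEM records how often symptoms occurred over seven days. DLQI measures quality of life, and PO-SCORAD is a separate severity score. Baseline POEM is therefore only a partial stand-in for either baseline. The article gives no reason for preferring it, and the better covariate is already in the database.

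The design does not make up for this: "randomisation will be stratified according to site", so no severity scale is balanced by stratification. At stake are wider confidence intervals for PO-SCORAD and DLQI, and estimates that in the realised trial move more with a chance difference in those scales' baselines.

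**Working it through.** **The plan's own figure.** With a difference of 3.4, SD 6.0, two-sided alpha 5% and 80% power, the exact t-test calculation gives 50 per group (power 80.1%; 49 gives 79.3%). Allowing for 15% loss, 100 / 0.85 = 117.6, so 118. The stated sample size reproduces. It concerns POEM, which is adjusted for its own baseline, and is not affected.

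**Inputs for the comparison.** The article gives no correlations, so all three are assumptions:
- r, own baseline with own week-6 score: 0.5 (range 0.4 to 0.6)
- p, baseline POEM with own week-6 score: 0.3 (range 0.2 to 0.4)
- q, baseline POEM with own baseline: 0.6

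**Residual variance, all scores scaled to variance 1.**
- Own baseline as covariate: 1 - r². This holds for the week-6 score and for change, since 2(1 - r) - (1 - r)² = 1 - r².
- Baseline POEM as covariate, week-6 score: 1 - p².
- Baseline POEM as covariate, change score: 2(1 - r) - (p - q)².

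**Central case.**
- Own baseline: 1 - 0.25 = 0.75.
- POEM, week-6 score: 1 - 0.09 = 0.91.
- POEM, change: 1.00 - 0.09 = 0.91.
- Variance ratio for either form: 0.91 / 0.75 = 1.21. Standard error ratio: √1.21 = 1.10.
- Equivalent sample loss: 1 - 0.75 / 0.91 = 0.18, or about 18 of the 100 evaluable participants planned.
- A comparison with 80% power under own-baseline adjustment would have about 72%.

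**Range (variance ratio, POEM covariate against own baseline, q = 0.6).**

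| r | p | Week-6 score | Change score |
|---|---|---|---|
| 0.4 | 0.2 | 0.96/0.84 = 1.14 | 1.04/0.84 = 1.24 |
| 0.4 | 0.4 | 0.84/0.84 = 1.00 | 1.16/0.84 = 1.38 |
| 0.5 | 0.3 | 0.91/0.75 = 1.21 | 0.91/0.75 = 1.21 |
| 0.6 | 0.2 | 0.96/0.64 = 1.50 | 0.64/0.64 = 1.00 |
| 0.6 | 0.4 | 0.84/0.64 = 1.31 | 0.76/0.64 = 1.19 |

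The inflation is 0-50% for a week-6 score and 0-38% for a change score. The two forms reach their extremes at different correlations, so the 50% figure must not be carried over to change.

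**A second set of assumptions.** Suppose instead that baseline POEM predicts week 6 only through the own baseline (p = q × r), with r from 0.3 to 0.7 and q from 0.5 to 0.8. The ratio is then 1.04 to 1.72 for a week-6 score and 1.06 to 1.40 for change.

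**Chance imbalance.** With 50 per arm, the difference between arms in a baseline mean has SD √(2/50) = 0.20 baseline SDs. At q = 0.6, conditioning on POEM leaves √(0.04 × (1 - 0.36)) = 0.16. This is the precision loss seen from another side and must not be added to it.

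**The case against.** **Validity is not in question.** A reader might infer that the PO-SCORAD and DLQI estimates are biased or the tests invalid. The article does not support that. "Participants are randomised 1:1 to receive a 2% ECMT-154 cream or vehicle control", and under randomisation, ANCOVA on any covariate measured beforehand is unbiased on average and keeps its type I error. A chance own-baseline imbalance shifts the estimate in one realised trial, but the standard error already allows for this. No power is claimed for either scale. This stands, and it makes the issue one of efficiency.

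**The wording may be shorthand.** One sentence in a condensed article covers several outcomes, and the SAP may name each scale's own baseline. That is possible, but the text as written names a specific covariate, and an analyst following it would fit that model.

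**SCORAD part B.** A reader might extend the point to SCORAD part B, which is absent from the ANCOVA sentence. The only SCORAD method given is for rater agreement: "Comparison of SCORAD scores between pharmacists and between pharmacist and dermatologist will be by linear mixed model with participant treated as a random effect". But no method for its treatment comparison is stated, so none is stated wrongly. The SAP may supply one, and no loss of precision can be shown.

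**Site.** Because site is the stratification factor, a reader may also want it in the model. That is a separate question, and nothing here depends on it.

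**Conclusion.** The point holds for PO-SCORAD and DLQI as a loss of efficiency from a covariate rule that the article states. At the central assumptions the loss is about 21% in variance and 10% in standard error, whichever outcome form is used. Its true size depends on correlations that the article does not give. It vanishes in some corners of the assumed range, for example where baseline POEM predicts the week-6 score as well as the scale's own baseline does. Because only secondary comparisons are touched, severity is minor to moderate. It is worth correcting because the better covariate is already collected.

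**What to change.** Reword the sentence so that PO-SCORAD and DLQI are each analysed by ANCOVA with the Visit 1 value of the same scale as the continuous covariate and randomised treatment as the factor. Baseline POEM may stay as an additional covariate. With the own baseline in the model, the treatment estimate is the same whether week-6 score or change is analysed, so that ambiguity stops mattering too. The same model can be named for the SCORAD part B treatment comparison, which also has a Visit 1 value.

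The cost is one sentence in the protocol or SAP, with no new data and no change to the sample size. It should be made before unblinding, so that the covariate is not chosen with results in view.

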### Trial setting and recruitment

This study will be conducted using the Medical Research Institute of New Zealand (MRINZ) Pharmacy Research Network (PRN), an established network of over 80 research trained community pharmacists in Aotearoa New Zealand overseen centrally by researchers at the MRINZ [52, 53]. Between 10–15 pharmacies will recruit participants and undertake study related procedures. Pharmacies were selected based on previous recruitment success and capacity to complete study procedures. Adults presenting to a PRN pharmacy seeking advice for eczema will be screened for eligibility. Advertising within participating pharmacies and on mainstream or social media will be used as a recruitment tool.

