#### Power calculation

The sample size calculation is based on a minimal clinically important difference (MCID) of 3.4 [62] and pooled standard deviation (SD) of 6.0 for the change in POEM score [52]. With 80% power, and 5% two-sided alpha, each treatment group would require 50 participants. Allowing for 15% withdrawal and loss to follow up, 118 participants total are required for this study.

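### Randomisation is stratified by pharmacy but the ANCOVA omits site; if pharmacies differ in outcome, the standard error is somewhat too large and the test mildly conservative

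*Protocol article*

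**What the plan says.** Under Randomisation and masking: "Participants are randomised 1:1 to receive a 2% ECMT-154 cream or vehicle control", and "Participants will be block randomised, block size four, and randomisation will be stratified according to site". Under Trial setting and recruitment: "Between 10–15 pharmacies will recruit participants and undertake study related procedures".

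Under Statistical analysis, the primary outcome and the secondary POEM, PO-SCORAD and DLQI outcomes are to be analysed by "ANCOVA with baseline POEM score as a continuous covariate", with "randomised treatment as a categorical variable of interest". Site appears in that model neither as a fixed nor as a random term, and no reason is given for leaving it out. The only random effect in the section is participant, and it belongs to the comparison of SCORAD raters.

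**The concern.** Blocking within site keeps the arms close to balanced in every pharmacy, so differences between pharmacies largely cancel out of the treatment contrast. If site is then left out of the model, those differences stay in the residual variance. The SE printed by the model is then larger than the true sampling variability of the estimate. Confidence intervals are wider than they need be, p-values are larger, and the two-sided test rejects less often than 5% under the null.

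What is at stake is efficiency. The trial is sized at barely 80% power, so a few points of power are worth having when they need only one added model term. The article names the model's terms itself, so this is a comment on a stated model and not on a detail left to a later document.

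**Working it through.** **Inputs from the article.** Power calculation: "minimal clinically important difference (MCID) of 3.4", "pooled standard deviation (SD) of 6.0 for the change in POEM score", "With 80% power, and 5% two-sided alpha, each treatment group would require 50 participants", 15% loss, 118 in total. Randomisation and masking: 1:1, blocks of four within site. Trial setting and recruitment: 10 to 15 sites. Statistical analysis: missing outcomes are not imputed.

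**The plan's own figure.** The normal approximation gives 2 × (1.960 + 0.842)² × 6.0² / 3.4² = 48.9, so 49 per arm. The noncentral t gives power 0.793 at 49 and 0.801 at 50, so 50 per arm. Then 100 / 0.85 = 117.6, so 118. Both stated figures reproduce. The matching SE is 6.0 × √(2/50) = 1.20 POEM points.

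**Idealised bound.** With perfect balance in every site and no cost of estimating site effects, leaving site out overstates the SE by the factor 1/√(1 − ICC). That is 1.026 at ICC 0.05 and 1.054 at ICC 0.10. Real blocks are left incomplete: 118 participants over 10 to 15 sites is about 8 to 12 each, before 15% loss. Simulation is therefore the better guide.

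**Simulation.** 118 randomised, 10 or 15 sites of unequal size, blocks of four within site, 15% loss at random, 6,000 replicates per setting. ANCOVA was fitted without site and with site as a fixed effect. Assumptions: the ICC, which the article does not give, and a total SD of 6.0 after baseline adjustment. Each cell gives the range over 10 and 15 sites. SE overstatement is mean model SE divided by empirical SE, for the model without site.

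| Assumed ICC | SE overstated | Type I error, without / with site | Power at 3.4, without / with site |
|---|---|---|---|
| 0 | none | 5.2% / 5.1-5.4% | 79-80% / 77-79% |
| 0.05 | about 1-2% | 4.5-4.6% / 5.0-5.1% | 80-81% / 79-82% |
| 0.10 | about 1-5% | 4.0-4.4% / 4.6-5.3% | 80-81% / 81-83% |
| 0.20 | about 6-9% | 3.7-3.9% / 5.1-5.2% | 82-83% / 85-87% |
| 0.30 | about 10-14% | 2.5-3.3% / 4.7-5.2% | 83-84% / 90-91% |

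Example at ICC 0.20 with 10 sites, under the null: 1.1827 / 1.1153 = 1.060, so 6% too large.

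Monte Carlo error is about ±0.6 points at 5% and ±1 point at 80%. An empirical SE from 6,000 replicates has a relative standard error of about 1/√12,000 = 0.9%, so the 1-2% at ICC 0.05 is not clearly different from zero.

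**Second simulation, same design figures.** At ICC 0.10 the SE was overstated by about 2-6%, and power was about 80-81% without site and 83% with a random intercept. At ICC 0.20 the SE was overstated by about 8-10%. At ICC 0 the random intercept cost essentially nothing, while fixed site effects cost about 1-2 points of power.

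**Both simulations together.** ICC 0.10: SE overstated by roughly 1-6%, type I error about 4-4.7%, gain about 0-3 points. ICC 0.20: roughly 6-10%, about 3.6-3.9%, gain about 3-5 points.

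**The case against.** The strongest defence is that leaving out site is a tolerable, conservative choice with many small strata. No ICC is stated, baseline POEM already absorbs part of any case-mix difference between pharmacies, and power under the planned model stays at about 79-84% throughout the table. With fixed site effects, adjustment loses 1-2 points of power if sites do not differ and gains nothing dependable at ICC 0.05. All of this stands. It makes the point conditional and minor, and it favours a random intercept over fixed effects.

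A reader might infer more than the article supports:

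- *That the test is invalid or the estimate biased.* It is neither. The error runs in the conservative direction.
- *That the SE is certainly overstated.* This holds only if sites differ beyond baseline POEM, and no figure in the article shows that they do.
- *That the precision gained by stratifying is thrown away.* The estimate keeps it, and only the reported SE fails to show all of it. So 80.1% power, which assumes no site effect, is the wrong comparator for a site-adjusted analysis. At ICC 0.10 with perfect balance, the unadjusted test already has about 81.3% power against 84.1% with site, a gain of just under 3 points.
- *That SCORAD part B suffers most because site and rater coincide.* The stated ANCOVA covers POEM, PO-SCORAD and DLQI only. The article names no between-arm model for SCORAD part B and does not say how many pharmacists rate at each site.

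**Conclusion.** The point holds as a conditional, minor one. The analysis does not follow the stratified design, and the consequence is a mildly conservative test if pharmacies differ in outcome beyond baseline POEM. It is negligible at an ICC of about 0.05 or less, small at 0.10 and worth a few points of power at 0.20. The direction is secure. The size rests on an assumed ICC, on loss unrelated to arm or outcome, and on a residual SD of 6.0. Neither the validity of the trial nor the sample size of 118 is in question.

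**What to change.** Add site, as the stratification factor, to the primary ANCOVA and to the secondary POEM, PO-SCORAD and DLQI models, preferably as a random intercept. If site is to stay out, give the reason in the text. The change should be fixed before unblinding. If a separate analysis plan already includes site, the two descriptions should be made to agree.

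The cost is one phrase in the Statistical analysis section and slightly more modelling work. A random intercept costs essentially no power if sites do not differ. Fixed site effects would use 9 to 14 degrees of freedom and lose about 1-2 points of power in that case; if they are chosen, a rule for pooling very small sites should be set in advance. The sample size is unchanged.

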### Permitted and prohibited concomitant treatment

No other eczema treatments or moisturisers will be permitted during the trial. Participants can continue with all other prescribed medication. Concomitant medication usage will be collected in the weekly participant diaries, which ask asked if participants have used any medications other than their study treatment in the last week, prompts them to leave details and MRINZ investigators will contact the participant directly to complete concomitant medication forms based on C-DASH standards. It is recognised that minor exacerbations of eczema are expected, therefore the usage of topical corticosteroids habitually used by the participant, for a duration of less than or equal to seven days, is permitted without requiring withdrawal from the study. The requirement for escalated treatment will be recorded and compared between treatment groups.

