### Outcome measures

#### Primary

Primary outcome is severity assessed by subjective symptoms over six weeks, measured by change in POEM scores, adjusted for baseline. The POEM tool assesses severity of eczema by capturing self-reported frequency of symptoms over the previous seven days [54]. Scores can range from 0 to 28, with higher scores indicating a higher severity of disease. The following bandings have been established: Clear or almost clear (0–2); Mild eczema (3–7); Moderate eczema (8–16); Severe eczema (17–24); Very severe eczema (25–28).

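### The primary analysis is labelled ITT but is in effect complete-case, and makes no stated use of the weekly POEM scores that could keep partly observed participants in

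*Protocol article*

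**What the plan says.** The Statistical analysis section of the protocol article says "ITT population is all participants randomised" and separates ITT from the per-protocol set "with ITT as the primary analysis". The primary analysis "will be by ANCOVA with baseline POEM score as a continuous covariate, and randomised treatment as a categorical variable of interest". It has no week term and no repeated-measures structure; the one mixed model in that section is for the SCORAD rater comparisons. On missing data it says "Missing outcome data will not be imputed".

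The Primary outcome section reads: "Primary outcome is severity assessed by subjective symptoms over six weeks, measured by change in POEM scores, adjusted for baseline". It names no single time point.

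On data collection, the Participant timeline section says "participants complete a weekly digital diary to report POEM, treatment adherence, adverse events, and use of concomitant medications". Table 2 schedules POEM at days 0, 7, 14, 21, 28, 35 and 42.

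Three places bear on loss of data:
- The Power calculation section reaches its total "Allowing for 15% withdrawal and loss to follow up".
- The Secondary outcomes include a count of participants who leave because their eczema gets worse.
- The section on concomitant treatment says that a participant's habitual topical corticosteroid, used "for a duration of less than or equal to seven days, is permitted without requiring withdrawal from the study". This implies, without stating it, that longer use may lead to withdrawal.

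**The concern.** The label and the method describe different sets of people. An ANCOVA with one outcome per participant cannot include someone whose outcome is missing unless the value is filled in, and the plan rules that out. What is called an analysis of all randomised participants is in effect an analysis of those with a final POEM.

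Such an analysis, adjusted only for baseline, is generally unbiased if loss depends on nothing beyond arm and baseline POEM. The protocol gives reason to doubt this for part of the loss: it counts exacerbation withdrawals and links longer corticosteroid use, by implication, to withdrawal. It also assumes that participants can tell their arm by smell, which is one way in which loss could differ between arms. A participant who worsens in week 3 and then leaves will usually have diary POEM scores that show it, but the primary model as stated does not use them.

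At stake is the main effect estimate, in a trial powered at 80% for a difference of exactly 3.4 points.

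**Working it through.** **Inputs from the protocol article.** Difference 3.4, SD of change 6.0, 80% power, two-sided 5%, 1:1 allocation, 15% withdrawal and loss, total 118 (Power calculation; Randomisation and masking). POEM weekly (Table 2).

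**1. The plan's own figures.** Normal approximation: n = 2 × (1.960 + 0.842)² × 6.0² / 3.4² = 48.9, so 49 per arm. The noncentral t calculation gives 50 per arm (power 0.801). Inflation: 100 / 0.85 = 117.6, so 118. Both stated figures reproduce.

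**2. Who leaves the primary analysis.** 0.15 × 118 = 17.7, about 18. The remaining 100 are the 2 × 50 on which the trial was sized, so the sample size already assumes an analysis of completers.

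**3. Algebra of the bias.** Let d be the proportion lost in an arm and g the number of points by which the lost participants' final change is worse than the completers'. The mean over everyone is the completers' mean plus d × g. With the same g in both arms, the estimated benefit is too small by (d_vehicle − d_active) × g.

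| Loss, active v vehicle | g = 3 | g = 6 | g = 9 |
|---|---|---|---|
| 15% v 15% | 0 | 0 | 0 |
| 10% v 20% | 0.3 | 0.6 | 0.9 |
| 5% v 25% | 0.6 | 1.2 | 1.8 |

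Swap the arms and the sign reverses: the benefit is overstated by the same amounts. All values of d and g here are assumptions.

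**4. Simulation.** Assumptions, none of them in the documents:
- 59 per arm, true difference 3.4, SD 6.0;
- autoregressive weekly correlation of 0.6, 0.8 or 0.9;
- all loss triggered by an observed worsening: more than 5 points with weekly dropout probability 0.25, or more than 4 points with 0.35;
- 1,500 runs per setting.

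These are the settings with overall loss between 10% and 20%. Estimates are shown as benefit. Shortfall is the full-data mean minus the complete-case mean.

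| Trigger, correlation | Lost, vehicle / active | Full data | Complete-case ANCOVA | Repeated measures | Shortfall |
|---|---|---|---|---|---|
| >5, 0.6 | 14.9% / 8.6% | 3.44 | 3.24 | 3.42 | 0.20 |
| >5, 0.8 | 14.1% / 8.0% | 3.39 | 3.07 | 3.39 | 0.32 |
| >5, 0.9 | 13.1% / 7.7% | 3.46 | 3.10 | 3.47 | 0.36 |
| >4, 0.6 | 24.6% / 15.0% | 3.40 | 3.11 | 3.40 | 0.29 |
| >4, 0.8 | 22.5% / 13.7% | 3.38 | 2.89 | 3.37 | 0.49 |
| >4, 0.9 | 20.7% / 12.8% | 3.31 | 2.77 | 3.32 | 0.54 |

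Measured against the nominal 3.4, the shortfall runs from 3.40 − 3.24 = 0.16 to 3.40 − 2.77 = 0.63, so about 0.2 to 0.6. Approximate power is 0.70–0.82 for complete-case ANCOVA and 0.76–0.87 for the repeated-measures estimate.

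**5. Milder mechanisms.** A second, similar set-up (about 12–19% missing, 2,000 runs per setting) mixed in ordinary loss. The bias was 0.20–0.34 points with all loss worsening-driven, 0.08–0.15 with half, 0.05–0.07 with a quarter, and about 0 with none. The bias is proportional to the excess loss in step 3, so halving the wider range of step 4 gives 0.2 / 2 = 0.1 to 0.6 / 2 = 0.3.

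**6. Bias against noise.** The estimate's standard error is about 1.1–1.2 points, so 0.34 is about 0.3 standard errors. The repeated-measures estimate is slightly more variable. At trigger >4 and correlation 0.8, root mean squared error is √(1.14² + 0.49²) = 1.24 for complete-case ANCOVA, against 1.19. The gain is mainly in bias, not in precision.

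**The case against.** A reader might infer that the plan drops participants withdrawn for worsening eczema. The documents do not say so. Nothing states that POEM collection stops at withdrawal. Table 1 allows the six-week follow-up by telephone, and diary non-responders get daily reminders. A withdrawn participant leaves the analysis only if no final POEM is obtained. Week 6 is likewise an inference from a six-week outcome and a one-outcome model.

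Nor can one say that the missing outcomes are those of people doing badly. The 15% pools withdrawal with ordinary loss to follow-up, and no split by cause or arm is given. The allowance for short corticosteroid use keeps some flaring participants in the study.

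It would also go too far to say that the weekly scores are collected and then ignored. A separate secondary outcome on the difference in POEM scores may use them; only the primary model makes no stated use of them.

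Further, the simulations in step 4 make all loss worsening-driven and heavier on vehicle. That direction is conservative for a superiority claim. Dropout there depends only on observed scores, which is the condition that suits a repeated-measures model. The no-imputation rule is not an error in itself, since the proposed model does not impute either. The plan states the rule openly and sizes the trial for the loss.

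All of this stands, and it limits the size and certainty of the point. It does not remove the mismatch between an all-randomised label and a method that cannot include people without a final score. An unseen SAP could add sensitivity analyses, but the protocol itself fixes the model and the missing-data rule.

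**Conclusion.** The point holds in a limited form. As written, the primary analysis is complete-case under an ITT label, excluding about 18 of 118 at the planned loss, while partial POEM data from days 7 to 35 have no stated role in it.

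The bias depends on assumptions that the documents cannot settle:
- about 0.2–0.6 of 3.4 points too small, if 10–20% are lost, all through worsening and more on vehicle;
- about 0.1 (0.08–0.15) in the milder set-up if half the loss is worsening-driven, or up to about 0.3 by halving the wider range;
- near zero if loss is balanced and similar in kind;
- the opposite sign if more active-arm participants leave while doing badly.

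The documents do not support a claim that the primary result will be seriously biased, or biased in a known direction. This is a change that should be made because it is cheap and rests on a weaker missing-data assumption. It is not a defect that invalidates the trial.

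**What to change.** Make the primary analysis a likelihood-based repeated-measures model on POEM at weeks 1–6, with treatment, week, treatment × week, baseline POEM, baseline POEM × week and an unstructured covariance. Name the week-6 treatment difference as the primary contrast. No imputation is needed, so that rule can stay. Keep the ANCOVA as a supportive analysis and describe it as complete-case.

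State that diary POEM and the final POEM are still sought, through the existing electronic links, from participants who stop the cream or are withdrawn, unless they decline. State how POEM recorded after escalated treatment is handled, because using those scores and modelling from earlier scores answer different questions.

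The model relies on data being missing at random, so add one missing-not-at-random sensitivity analysis, for example a delta adjustment for exacerbation withdrawals.

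Cost: protocol and SAP wording, some SAS code, a few more reminders and a slightly more complex model. N stays at 118 and no visits are added. The change should be documented before unblinding.
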